### Interventions

#### Intervention arm

The cricoid operator will stand on a set of scales with a visible display providing direct feedback of the force applied to the cricoid while performing CP. When required, the operator will apply 30 - 40 N force (equating to a weight displacement of 3.060 - 4.075 kg [29]) to the cricoid during RSI unless otherwise instructed by the intubation operator. Force will be applied until the endotracheal tube (ETT) placement is confirmed by end tidal CO_2 _and the ETT cuff is inflated.

#### Control arm

The cricoid operator will stand on a set of scales while performing CP. The scale display will be covered to blind the operator to the amount of force they are using. When required, the cricoid operator will apply what they consider to be 30 - 40 N force to the cricoid during RSI unless otherwise instructed by the intubation operator. Force will be applied until the ETT placement is confirmed by end tidal CO_2 _and the ETT cuff is inflated.

### Outcome measures

#### Primary outcome measures

• Rate of aspiration (pepsin detection in tracheal aspirate)

• Treatment for aspiration pneumonitis

#### Secondary outcome measures

• Grade of laryngeal view

• Detection of pepsin in oropharyngeal aspirates

• Procedural complications associated with intubation

• Immediate complications (associated with RSI) within 30 minutes of intubation

• Lowest pre-intubation GCS

• Survival to 28 days/hospital discharge

### Methods

#### Cricoid pressure measurement

A platform scale with pole-mounted liquid crystal display LCD (150 kg capacity) set to record in 0.01 kg increments is used to measure cricoid pressure (Figure 1. Model PT270, PT Global Pty Ltd., NSW, Australia). The scale is mounted on a hand trolley with a custom made extended toe plate (designed to support the base plate of the scale without interfering with its levelling feet) allowing it to be easily manoeuvred into position next to the resus bed when required. Once in position and turned on, the cricoid operator stands on the scale and select the tare option to display their body weight as zero. Direct feedback of the force applied to the cricoid is available via the displayed weight reduction (a reading of -1 kg equates to approximately 10 N force). The cricoid operator maintains contact only with the scale baseplate and the patient's cricoid cartilage during the procedure to ensure the weight displayed accurately reflects the amount of their body weight transferred through the patient's cricoid.

**Figure 1 F1:**
[figure not shown]
**Platform scale with pole mounted display and serial data logger connected, secured to a hand trolley**.

Weight data is collected from the time the cricoid operator stands on the scales via a serial data recorder (model SDX, Photologic Ltd., Ottawa, Canada) onto a 2 gigabyte Secure Digital (SD) card. The scales transmit at a rate of 60 data points per second.

#### Pepsin assay

Ufberg's pepsin plate assay is reliant upon test samples containing enzymatically active pepsin. Pepsin activity is highly sensitive to pH with maximum activity between pH 1.5-2.5 and irreversible inactivation occurring above pH 7.5 [43]. Pepsin stored in gastric juice samples at 4°C remains active for up to 3 days (evaluated up to pH 6)[44]. The pH of saliva sampled from patients following episodes of gastric regurgitation has been reported to range from 7-8 [45]. Therefore citric acid (pH 2.5) will be added to aspirates to ensure pepsin activity is maintained prior to testing.

The laboratory will perform the qualitative pepsin plate assay based on fibrinogen digestion according to the method of Ufberg *et al*. [39]. Briefly, 1.25% agarose plates are prepared with bovine fibrinogen (in normal saline) added to a final concentration of 1 mg/ml. Four wells are punched into the agarose, each capable of holding 7 μl of test sample. Porcine pepsin (positive control) and normal saline (negative control) are included on each plate along with a sample of each aspirate from one patient. The plates are left in a humid chamber for up to 24 hours when they are read by visual inspection. A positive result is recorded if there is visible clearing zone around a well. No clearing zone visible after 24 hours is recorded as a negative result. The plate is checked progressively after sample addition initially every 2 hours, in this way a positive tracheal result can be communicated to the clinician.

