### Data collection

After the intubation is complete the personnel involved complete a data sheet included in the trial enrollment pack. Data recorded includes patient demographics, procedural details, procedural and post-intubation complications encountered.

*Patient demographic details*; age, date & time of intubation and medical record number (for 28 day follow-up).

*Procedural details*; location of intubation (ED or pre-hospital), lowest pre-intubation GCS, intubation drugs used, experience of intubation operator, evidence and nature of macroscopic aspirate seen and grade of laryngoscopic view obtained.

*Procedural complications*; 3 or more attempts to place the ETT in the trachea, > 10 minutes using conventional laryngoscopy, required change of operator, termination of the attempt at RSI, use of laryngeal mask or surgical airway.

*Post-intubation complications encountered within 30 minutes of RSI*; severe hypotension (Systolic blood pressure < 60 mmHg), severe hypoxaemia (SaO_2 _< 70%), death and cardiac arrest.

The data sheet and SD card containing weight data will be sent to the Trial Coordinator who will enter the data into a password-protected database. Each episode of RSI has a unique randomly assigned number within the database (Plate Number). This number will be linked to the episode of service, and the pepsin assay result will be automatically appended to the corresponding patient data set in the database. The investigators are therefore blinded to the results coming in from the laboratory.

At 28 days the patient notes will be reviewed. The acute physiology and chronic health evaluation (APACHE II) score and diagnostic code will be determined and any treatment for aspiration as an inpatient (discharge diagnosis of aspiration pneumonitis/pneumonia or antibiotic therapy explicitly instituted to treat for aspiration pneumonia) will be noted.

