### Sample processing

The aspirates are sent directly to the hospital's pathology laboratory for pepsin detection or, if outside pathology opening hours, stored at 4°C until the laboratory opens. Tamworth and Port Macquarie hospitals have access to a 24 hour pathology laboratory, while Coffs Harbour hospital's pathology service operates between 0700-2400 hours. Each laboratory is blinded to the conduct of CP during the intubation.

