## Discussion

The primary aim of this study is two-fold. Firstly, by comparing the incidence of aspiration of pepsin in the intervention and control groups and prospectively documenting the benefits and adverse events associated with 30 - 40 N of cricoid force during RSI, it aims to challenge the notion that CP prevents aspiration. Secondly, since the presence of pepsin in the oropharynx will be indicative of aspiration having occurred prior to intubation by virtue of the injury sustained by the patient, determining the incidence of pre-intubation aspiration will allow us to further evaluate the relevance of CP in the RSI algorithm in ED.

The secondary aim of this study is also two-fold. Firstly, defining any observed correlation between aspiration and pre-intubation Glasgow coma score will provide evidence for indications for the use of CP dependent upon the level of patient consciousness. Secondly, a correlation between detection of pepsin in trachea and development of aspiration syndromes will support the use of Fibrinogen plate assay in a clinical setting for their early detection and treatment.

It is conceivable that this research could also give rise to novel therapy. For example, once the incidence of serious aspiration and a pepsin positive assay is identified, the plate assay for pepsin could potentially be performed at the bedside, enabling doctors to treat aspiration pneumonia much earlier. It may also lead to amendments to the algorithm for RSI if CP is found to be deleterious.

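### A correlation between a yes/no pepsin result and an undated aspiration syndrome carries no lead time, so it cannot by itself support early detection

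*Protocol article*

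**What the plan says.** All references are to the protocol article.

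- **Secondary aims.** The stated aim is to look for a correlation between pepsin in aspirates and clinical aspiration syndromes. No aim concerns time to detection.
- **Discussion.** A correlation between tracheal pepsin and these syndromes "will support the use of Fibrinogen plate assay in a clinical setting for their early detection and treatment". A later, openly speculative sentence imagines bedside use and earlier treatment.
- **Pepsin assay.** "The laboratory will perform the qualitative pepsin plate assay based on fibrinogen digestion". The rule for a positive reads: "A positive result is recorded if there is visible clearing zone around a well". The rule for a negative reads: "No clearing zone visible after 24 hours is recorded as a negative result". On the reading schedule: "The plate is checked progressively after sample addition initially every 2 hours, in this way a positive tracheal result can be communicated to the clinician". Reading is thus not confined to the 24-hour point.
- **Data collection.** Time of intubation is listed. For the assay, "the pepsin assay result will be automatically appended to the corresponding patient data set in the database". At 28 days the notes are reviewed for a discharge diagnosis of aspiration or for antibiotics given specifically for it. No date of onset, diagnosis or first treatment is listed.
- **Sample processing.** Two sites have 24-hour laboratories. At the third, "Coffs Harbour hospital's pathology service operates between 0700-2400 hours", and specimens are refrigerated until it opens.

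**The concern.** Early is a statement about time, and a correlation between two undated yes/no variables contains none. An accurate assay brings no gain in earliness if it turns positive after the clinicians have already diagnosed or treated the patient. As described, the trial could find a strong correlation and draw its stated conclusion without any evidence on which event came first.

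There is a second difficulty. The laboratory may tell the clinician about a positive tracheal result while the plate is still incubating, and antibiotics started for aspiration are part of what defines the syndrome. Some of the correlation could then be produced by the reporting itself. Only the times of reporting and of treatment can separate this from a true forecast.

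**Working it through.** **The plan's own figure.** The only statistical figure is 106 per group. It reproduces, and this point does not depend on it. Inputs from the Sample size section: 11% v 0%, power 90%, alpha 0.05 (two-sided assumed). The mean proportion is 0.055.

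- n = [1.960 × √(2 × 0.055 × 0.945) + 1.282 × √(0.11 × 0.89)]² / 0.11² = (0.632 + 0.401)² / 0.0121 ≈ 88.2, that is 89 without continuity correction.
- With correction: (88.2 / 4) × [1 + √(1 + 4 / (88.2 × 0.11))]² ≈ 105.6, that is 106.

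**When a result can be known.** Inputs: first check about 2 h after plating, final reading at 24 h, one laboratory closed from 2400 to 0700. Transport time is ignored.

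| Case | Wait before plating | First check after sampling | Final reading after sampling |
|---|---|---|---|
| Laboratory open | about 0 h | about 2 h | about 24 h |
| Specimen taken at 0001, third site | about 7 h | 7 + 2 = about 9 h | 7 + 24 = about 31 h |

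The 31 h figure is the latest time at which a plate can still be called positive, and the time at which a negative is declared.

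**What the listed variables can distinguish.** Lead time = (time of first clinical diagnosis or treatment) − (time positivity was seen). Neither term is among the variables listed. Take two patients both treated T hours after plating, with T between 2 and 22. One plate clears at 2 h, giving a lead of T − 2, which is positive. The other clears at 22 h, giving T − 22, which is negative. Both are stored identically as assay positive, syndrome present.

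**Order of events.** Three sequences give that same record:

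1. Plate positive, result reported, treatment started because of the report.
2. Plate positive, treatment started later on clinical grounds.
3. Treatment started on clinical grounds, plate positive afterwards.

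Only the second shows the assay anticipating an independent clinical diagnosis.

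**How many events could inform this.** Under the plan's assumption, 0.11 × 106 = 11.7, so about 12 aspiration events in the control arm and none in the other. If all 12 contributed and half were positive first, the standard error would be √(0.5 × 0.5 / 12) = 0.144, and the approximate 95% half-width 1.96 × 0.144 = 0.28, or 28 percentage points. Over the range of rates that the article cites (0.8% to 22%), 212 patients would give 0.008 × 212 = 1.7 to 0.22 × 212 = 46.6 events. Patients with both a positive assay and a syndrome would be no more numerous than this.

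**The case against.** The strongest reply is that a condensed article does not reproduce the laboratory form. It defines positive and negative but nowhere says that times are discarded, and plates are checked repeatedly from 2 hours on, so positivity is observed in time. That stands: a reader might infer that clearing times are thrown away, and the document does not support this. It does not rescue the inference in the Discussion, which rests on correlation alone whatever the form holds.

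A reader might also infer that earliness can never be shown. That is too strong. Positivity is bounded at roughly 24 to 31 hours after sampling, while follow-up runs to 28 days. If dates were recovered from the notes, a syndrome first recognised after that bound would necessarily follow its positive plate. The bound is uninformative for syndromes recognised within the first day or so, and no date is listed against which to apply it.

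It is fair, too, that the formal aim is correlation and that the bedside remarks are hedged. The sentence quoted from the Discussion is not hedged, and it sits with the secondary aim.

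Finally, recorded times would not give a clean lead time, because a reported positive can itself trigger treatment. This also stands, and is why the reporting time is needed and why the analysis should stay descriptive. Treating speed of clearing as a graded measure of pepsin would go too far: the assay is described as qualitative and nothing in the article links speed to amount.

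**Conclusion.** The point holds in a limited form. The step from correlation to early detection does not follow from the data described, because neither the time of positivity nor the time of clinical diagnosis or treatment is listed. Reporting positives to clinicians makes the order of events matter for interpreting the correlation as well.

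Its size is small. It touches one secondary aim and the sentence that interprets it. A reader might infer that the primary comparison is compromised, since treatment for aspiration pneumonitis is also a primary outcome measure. The timing argument does not show that: the same reading and reporting rule applies in both arms, the laboratories are blinded to how cricoid pressure was applied, and 106 per group reproduces.

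The conclusion assumes that the article's list of variables is a fair account of what is collected. The 9 and 31 hour figures are a worst case for one site and ignore transport. The document gives no distribution of time to clinical diagnosis, so how often a positive would come too late is unknown.

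**What to change.** 1. Have the laboratory record the plating time, the check at which clearing was first seen and the time any positive was reported to the clinician.
2. At the existing 28-day notes review, record the date and time of the first aspiration diagnosis or treatment.
3. Report descriptively how often positivity preceded the clinical diagnosis, separating treatment started before from treatment started after the result was reported.
4. Otherwise, limit the Discussion's conclusion to association.

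The cost is a little more laboratory and chart recording, at plate checks and a review that already take place. Overnight gaps will remain at the site whose laboratory closes, and with few expected events the estimates will be imprecise. The trial is listed as ongoing, and a clearing time not written down when seen cannot be recovered later, so the laboratory part is best started promptly.

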**Methods/design:**

212 patients requiring emergency intubation will be randomly allocated to either control (unmeasured cricoid pressure) or intervention groups (30 - 40 newtons cricoid pressure). The primary outcome is the rate of aspiration of gastric contents (determined by pepsin detection in the oropharyngeal/tracheal aspirates or treatment for aspiration pneumonitis up to 28 days post-intubation). Secondary outcomes are; correlation between aspiration and lowest pre-intubation Glasgow Coma Score, the relationship between detection of pepsin in trachea and development of aspiration syndromes, complications associated with intubation and grade of the view on direct largyngoscopy.

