#### Secondary aims

• Determine whether a relationship exists between the incidence of aspiration and pre-intubation Glasgow coma score (GCS).

• Determine any correlation between pepsin detection in aspirates and development of clinical aspiration syndromes.

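### A positive tracheal pepsin result may reach the clinician whose diagnosis or antibiotic decision then defines clinical aspiration, so the pepsin–syndrome correlation is biased upward

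*Protocol article*

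**What the plan says.** All references are to the protocol article.

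- **Pepsin assay:** plates are checked during the incubation of up to 24 hours, initially every 2 hours, and "in this way a positive tracheal result can be communicated to the clinician".
- **Data collection:** clinical aspiration is taken from the 28-day review of the notes as "discharge diagnosis of aspiration pneumonitis/pneumonia or antibiotic therapy explicitly instituted to treat for aspiration pneumonia". The same section says "The investigators are therefore blinded to the results coming in from the laboratory".
- **Primary outcome measures:** "Treatment for aspiration pneumonitis" has its own bullet, beside tracheal pepsin. The Abstract (Methods/design) instead gives one either/or outcome: pepsin in an aspirate, or "treatment for aspiration pneumonitis up to 28 days post-intubation".
- **Secondary aims:** "Determine any correlation between pepsin detection in aspirates and development of clinical aspiration syndromes". Study design describes the longitudinal follow-up as serving this purpose.
- **Discussion:** "a correlation between detection of pepsin in trachea and development of aspiration syndromes will support the use of Fibrinogen plate assay" in clinical practice.
- **Sample processing:** each laboratory is blinded to how cricoid pressure was conducted.

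**The concern.** To judge whether tracheal pepsin predicts aspiration syndromes, the syndrome has to be established independently of pepsin. Here both routes to a recorded syndrome are decisions of treating clinicians, and the plan allows those clinicians to learn that the tracheal sample was positive. A clinician told this is plausibly more likely to write the diagnosis or to start antibiotics labelled as being for aspiration. An association can then appear even if pepsin carries no information about clinical course.

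The Background notes that earlier work with this assay lacked follow-up linking pepsin to later syndromes. Filling that gap is a stated purpose of this trial, and a correlation partly made by disclosure would not fill it. Treatment for aspiration, if reported as a second primary outcome, would also look like independent clinical confirmation of the pepsin result when part of it is an echo of that result.

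**Working it through.** **The plan's own figure.** The article gives no figure for this point. Its only calculation is the sample size: 11% v 0%, 90% power, alpha 0.05, 106 per group. Taken as two-sided, the uncorrected formula gives

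n = [1.960·√(2·0.055·0.945) + 1.2816·√(0.11·0.89)]² / 0.11² ≈ 88.2 (89 rounded up).

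The continuity correction gives (88.2/4)·[1 + √(1 + 4/(88.2·0.11))]² ≈ 105.6, so 106. The figure is reproduced, and nothing below changes it.

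**Effect on the pepsin–syndrome correlation.** Let *s* be the background probability of recorded treatment, the same whatever the pepsin result (no true association). Let *c* be the share of otherwise untreated tracheal positives who are treated because of the result. Both are assumptions; the article gives neither.

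- P(treated | positive) = s + (1 − s)·c
- P(treated | negative) = s

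| s | c | Positive | Negative | Ratio |
|---|---|---|---|---|
| 10% | 0 | 10% | 10% | 1.0 |
| 10% | 5% | 0.10 + 0.90·0.05 = 14.5% | 10% | 1.45 |
| 10% | 10% | 0.10 + 0.90·0.10 = 19% | 10% | 1.9 |
| 10% | 25% | 0.10 + 0.90·0.25 = 32.5% | 10% | 3.25 |
| 10% | 50% | 0.10 + 0.90·0.50 = 55% | 10% | 5.5 |
| 5% | 25% | 0.05 + 0.95·0.25 = 28.75% | 5% | 5.75 |
| 5% | 50% | 0.05 + 0.95·0.50 = 52.5% | 5% | 10.5 |

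Every ratio above 1.0 arises with no real association.

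**Effect on the either/or composite.** A patient treated because of a positive tracheal result already counts through pepsin. Prompted treatment adds no event.

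**Effect on treatment as a separate outcome, between arms.** Let p be the tracheal-positive rate in each arm, with s and c common to both. The treatment rate in an arm is s + p·(1 − s)·c, so the difference is (p_control − p_intervention)·(1 − s)·c. This is zero when pepsin rates are equal. At the planned 11% v 0%, with s = 10%, prompted treatment adds 0.11·0.90·0.25 = 2.5 percentage points to the control arm (c = 25%) or 0.11·0.90·0.50 = 5.0 points (c = 50%). With s = 5% the additions are 2.6 and 5.2 points. A real pepsin difference would thus reappear in part as a treatment difference; no difference is invented.

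**The case against.** Several points from the other side stand.

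- **The randomised comparison is largely protected.** Laboratories are blinded to cricoid pressure, and one reporting provision covers both arms. A reader might infer that the primary comparison is biased. The documents do not support that for the either/or composite, nor for treatment alone when pepsin rates are equal.
- **The two sections do not strictly contradict each other.** A reader might infer that releasing results to the clinician makes the investigator-blinding statement false. One sentence concerns the clinician and the other the investigators, and nothing says they are the same people. They conflict only where an investigator also treats the patient, or where the 28-day reviewer finds the result in the notes. The article does not say whether either happens.
- **The text does not say that only positives are passed on.** It says a positive result can be communicated. It does not say that this is routine or that negatives are withheld.
- **Some treatment decisions may precede the result.** Plates can take up to 24 hours, and overnight samples at one site wait for the laboratory to open. This would dilute the effect.
- **The article is a condensation.** Reviewer masking and adjudication criteria may sit in the full protocol, so their absence here is not itself a fault.

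The last point does not dispose of the concern. The disclosure provision, the outcome definition and the intended use of the correlation are all stated, and together they produce the bias. Blinding investigators and laboratories does not blind the clinicians who make the diagnosis or start treatment.

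**Conclusion.** The concern holds within limits. As written, the plan lets the assay result influence the diagnosis or treatment against which the assay is judged. That biases the pepsin–syndrome correlation, a secondary aim, upward. It also makes treatment for aspiration partly dependent on the pepsin result where the Primary outcome measures list is read as naming it separately.

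The direction rests on one assumption: a clinician told of a positive result is more likely to diagnose or treat aspiration. The size cannot be stated, because the article gives no background treatment rate and no rate at which results are passed on or acted upon. With 10% background treatment, illustrative ratios run from 1.45 to 5.5 as the prompted share runs from 5% to 50%. These show what is possible and are not estimates. Until this is dealt with, a positive treatment-based correlation from this trial could not by itself support clinical use of the assay.

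**What to change.** 1. In the Pepsin assay and Data collection sections, state who may see assay results and who is blinded to them. The reporting rule itself is for the sponsor.
2. For the pepsin–syndrome analysis, have the existing 28-day notes reviewer, masked to pepsin result and allocation, classify aspiration syndromes on prespecified clinical and radiographic criteria. The criteria should exclude both the pepsin result and the treatment given, and should apply identically to every patient over the same 28 days.
3. Log whether and when each result was communicated, and when aspiration treatment or diagnosis was first recorded.
4. Report the treatment-based correlation only as a secondary result, split by whether the result was communicated, and do not rest support for the assay on it alone.

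Counting only syndromes recorded before communication is not a good substitute. Notified positives would have a case window of hours while everyone else kept 28 days, and most discharge diagnoses in notified patients would be lost. That would bias the correlation in the opposite direction.

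**Cost:** somewhat more chart abstraction, the work of writing the criteria, and a few time fields. Some patients treated without objective findings would not count in this analysis. Masked classification removes the influence of the result on labelling; it cannot undo any effect that treatment started on the result has on later clinical course, which is a further reason for the log. Sample size stays at 106 per group.
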